# Research for development (R4D): Health systems governance for an inclusive and sustainable social health protection in Ghana and Tanzania - Phase 2; Sub Study: Implementation of health financing policy and social health protection schemes in Tanzania

## Executive Summary

The Ifakara Health Institute, in collaboration with the Swiss Tropical and Public Health Institute, is seeking ethical clearance for the below protocol investigating the accessibility of NCD care in Tanzania, as a sub-study in the second phase of the Research for Development (R4D): Health systems governance for an inclusive and sustainable social health protection in Ghana and Tanzaia. Chronic non-communicable diseases (NCD), especially cardio-metabolic disorders such as hypertension and diabetes, are on the rise in sub-Saharan Africa. However, health systems in sub-Saharan Africa are mainly equipped for acute episodic treatment, and as such are ill-equipped for the successful treatment of non-communicable, chronic conditions. As such, the objectives of this protocol are to explore the implementation of health financing strategies particularly related to geographic accessibility of NCD care, economic barriers, willingness to pay for access to chronic disease care, and engagement in chronic care. This protocol will utilise both secondary and primary data to meet these objectives, and will begin by analysing secondary data provided by the National Health Insurance fund in order to provide an overview of NCD care provision in Tanzania and build a geospatial model of NCD care accessibility across Tanzania. Primary data will then be collected by recruiting households and patients to participate in surveys in order to better understand the costs of accessing NCD care, predictors of disengagement from care, and the willingness-to-pay for NCD care. Quantifying patient access and utilization of NCD care in Tanzania will provide crucial evidence for health systems strengthening efforts to provide NCD care in Tanzania, the importance of which will only increase as the burden of NCDs continues to rise due to demographic changes and urbanisation. In doing so, this study seeks to improve the equity of access to chronic care and inform the improvement of health financing policy and implementation so that Tanzania may work towards achieving a more inclusive, sustainable, and equitable health system and social health protection system.

# Abbreviations

| COSTECH | Tanzania Commission for Science and Technology |
| --- | --- |
| DHIS2 | District Health Information System 2 |
| EKNZ | Ethikkommission Nordwest- und Zentralschweiz |
| iCHF | Improved Community Health Financing |
| iHEA | International Health Economics Associated |
| IHI | Ifakara Health Institute |
| IRB | Institutional Review Board |
| MoHCDGEC | Ministry of Health, Community Development, Gender, Elderly and Children |
| NCD | Non-Communicable disease |
| NHIF | National Health Insurance Fund |
| NIMR | Tanzanian National Institute for Medical |
| OOP | Out of Pocket expenditures |
| PoRALG | President’s Office, Regional Administration and Local Government |
| R4D | Research For Development |
| SDC | Swiss Agency for Development and Cooperation |
| SNF | Swiss National Science Foundation |
| Swiss TPH | Swiss Tropical and Public Health Institute |
| WHO | World Health Organization |

# Introduction and Literature Review

Chronic non-communicable diseases (NCD), especially cardio-metabolic disorders such as hypertension and diabetes, are on the rise in sub-Saharan Africa. However, health systems in sub-Saharan Africa are mainly equipped for acute episodic treatment, and as such are ill-equipped for the successful treatment of chronic conditions [1]. This rapid epidemiological transition in the contribution of NCDs to the burden of disease in Africa has made it difficult for health systems to adapt to the challenge of financing and delivering costly chronic care. In Tanzania, several studies have evaluated the readiness and capacity of the health system to deliver chronic care, and have found very limited capacity in rural and primary care facilities in particular [2,3]. The lack of funding, and the inequitable allocation of funding for NCDs has exacerbated human resource challenges, and contributed to the poor availability of NCD diagnosis and care services outside major towns and urban centres [4]. The poor availability of NCD care at the primary care level has contributed to poorer health outcomes for Africans with NCDs, with age-standardised mortality attributable to NCDs being up to three times higher among sub-Saharan African populations, than among European ones. Therefore, these issues justify an in-depth investigation into the accessibility of NCD care in Tanzania, with the objective of identifying key barriers to NCD care accessibility and delivery, and making policy recommendations for strengthening and improving the delivery of NCD services in Tanzania.

# Statement of Problem, and Rationale

Quality NCD care is frequently unavailable at health facilities serving non-urban areas [2,3], 2014), and only approximately 32% of the population is covered by social health protection [5]. These issues increase the cost and difficulty of regularly accessing NCD care, so quantifying patient access and utilization of NCD care in Tanzania will provide crucial evidence for health systems strengthening efforts to provide chronic care.

National health Insurance Fund (NHIF) claims would provide a comprehensive record of healthcare received for NHIF beneficiaries, which can provide insight into the breadth and availability of NCD and other healthcare services that are available in Tanzania. While the NHIF only insures approximately 7% of the population [6], its comprehensive benefits package and nation-wide coverage jurisdiction make its claims database ideal for assessing healthcare provision, and otherwise costly chronic NCDs in particular [7]. Household surveys and health facility exit interviews will allow the in-depth investigation of health care utilisation, and the associated costs and structural challenges to using social health protection schemes to access care as reported by patients.

The current research proposal (R4D phase 2 Sub-study) will specifically explore the implementation of health financing strategies particularly related to geographic accessibility of NCD care, economic barriers, willingness to pay for access to chronic disease care, and engagement in chronic care. In doing so, this study seeks to improve the equity of access to chronic care and inform the improvement of health financing policy so that Tanzania may work towards achieving more equitable financing schemes inclusive of vulnerable and marginalized population groups.

# Objectives and Research Aims

Given the importance of health financing for access to and appropriate utilization of care, especially for chronic conditions, we are submitting a sub-study of the previously accepted protocol, “Health systems governance for an inclusive and sustainable social health protection in Tanzania.” The overall aim of our study is to explore the implementation process of health financing policy and social health protection schemes in Tanzania. In doing so, this study seeks to improve the equity of access to chronic care and inform the improvement of health financing policy so that Tanzania may work towards achieving more equitable financing schemes inclusive of vulnerable and marginalized population groups. In this phase of the study, we will expand upon the specific study objective *to identify challenges hindering the existing social health protection schemes from enabling poor and vulnerable groups accessing quality health care* with four specific objectives:

1. to quantify the direct and indirect cost associated with accessing NCD care services, and describe strategies for coping with the cost burden
2. to understand the differences between people with NCDs who are engaged in care and those that are not

To address these aims we will investigate the following research questions.

### Research Question 1

The second research question will aim to quantify the direct and indirect cost associated with accessing NCD care services, and describe strategies for coping with the cost burden. This includes determining which support systems people living with NCDs utilise, including their social networks, to cope with these costs. It will also seek to determine the cost of not having social health protection by comparing the total costs incurred between NHIF beneficiaries, iCHF beneficiaries, and those who are not part of a social health protection scheme. The role of patient social networks will be especially important to investigate, as it has been reported that people often attempt to capitalise on their social networks to avoid out-of-pocket expenditure (OOPs) by being added to another household’s iCHF membership, or by borrowing money from their social network [8]. Furthermore, this objective will take into account that although beneficiaries of social health protection may be less likely to experience financial hardship due to the direct cost of their illness, their illness may still impose a social and economic burden in the form of missed work days and lost income for either the individual living with the NCD, or their caregiver at times when one’s illness prevents them from working [9].

### Research Question 2

The third research question aims to understand the differences between people with NCDs who are engaged in care and those that are not. We aim to identify the proportion of the population that remains undiagnosed, and undertreated for hypertension and diabetes, and the barriers or perceived barriers to appropriately utilising NCD treatment compared with the patients who are accessing NCD care. In addition to socio-demographic and geographic mediators of care utilisation, we will quantify the willingness-to-pay for chronic disease care under different payment options, specifically out-of-pocket payments versus the payment of health insurance premiums, for both patients and individuals in the community.

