### Sampling Strategy and Sample Size

#### *Household survey*

We will conduct a household survey to collect information on household demographic and economic characteristics, health insurance and social protection, chronic illness, healthcare access and utilisation, household health expenditure, out of pocket payments for health care, and coping strategies to deal with diseases. In order to answer the key research question, information will be collected regarding direct and indirect household out-of-pocket expenditure (OOPs) on healthcare, how the household pays for their OOPs or social health protection premiums, economic productivity loss due to illness, recent healthcare utilisation, and the role of one’s social network in coping with illness. For respondents that accept, we will also measure blood pressure and random blood sugar to quantify undiagnosed and untreated hypertension and possible diabetes in the population. We will counsel patients with results outside of the normal range of the importance of following up with a healthcare provider to formally diagnose and initiate treatment if needed.

Using a stratified sampling approach, a household survey will be delivered throughout Kilombero and Same districts. In order to detect associations with the primary outcome of household health expenditure (power of 0.80, significance level of 0.05), a minimum sample size of 202 households per district is required. To calculate the minimum sample size, a household health expenditure of 30,000 Tanzanian shillings was used as a benchmark; corresponding to the cost of enrolling a household in the iCHF. However, in order to also answer research questions associated with our secondary objectives, we will seek a total sample size of 390 households per district.

As such, in each of Kilombero and Same district, 15 households from each district’s only town (Ifakara and Same, respectively), and 15 households from a random selection of 25 other villages will be sampled (Table 1).

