### Analytical Methods

By delivering a household survey to the general populations of Kilombero and Same, and an exit survey to people accessing NCD services, we will be able to comparatively analyse the specific challenges and coping mechanisms that people living with NCDs face in accessing services, in relation to the general population.

The data collected from the household survey and exit survey will first be analysed using descriptive statistics to investigate the burden of OOPs and economic losses associated with living with hypertension and/or diabetes, and to determine how much households spend upon the direct and indirect costs of accessing NCD care. General hypotheses related to the geographic and economic accessibility of health care, such as whether distance from a health facility is associated with direct and indirect healthcare costs, and whether distance from a health facility moderates the association between social health protection and household health expenditure, will be explored using linear mixed models and analyses of variance.

We will quantify the proportion of the household survey respondents who were hypertensive or diabetic, and not aware of their condition or not enrolled in care. We will then use univariate and multivariate logistic regression analyses to identify differences between the household respondents with an NCD who are not enrolled in care and NCD patients from the exit interviews who are enrolled in care. We will quantify systematic and individual characteristic predictors of willingness-to-pay for NCD care and social health protection schemes for people in care for non-NCD reasons, for NCD reasons, and household respondents.

A regression model will then be used to assess whether living with hypertension and/or diabetes is associated with financial hardship, and/or illness-related economic and productivity losses, using the indicators catastrophic health expenditure and impoverishment. An analysis of variance (ANOVA) of mean spending by revenue source will then be used to determine the relative importance of financial contributions from various household revenue streams to covering the costs of NCD care, such as:

- Earnings from work (informal or formal)

- Selling personal property (clothing, bicycle, furniture, etc.)

- Financial contributions from the social network (friends, family, neighbours, etc.)

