# Annex I

## Tables of requested variables NHIF

| Variable from NHIF Claims | Type | Category Breakdown |
| --- | --- | --- |
| Anonymized Identification Number | Numerical |  |
| Birthdate | Date |  |
| Gender | Category | Male, Female |
| Claim value | Numerical |  |
| Treatment date | Date |  |
| Facility Name | String |  |
| Facility Ownership | Category | Faith Based, government, non-government, private |
| Facility Level | Category | Accredited drug dispensing, Dispensary, District hospital, health centre, national referral hospital, pharmacy, regional referral hospital, specialized clinics, laboratories and diagnostic, zone referral hospital |
| Ward | Category |  |
| District | Category |  |
| Region | Category |  |
| Services Type | Category | Medicine and Consumables, Diagnostic Examinations |
| Service Detail | String |  |
| Funeral/Death Expenses | Numerical | Will be used to assess mortality |
| Life Insurance payout | Numerical | Will be used to assess mortality |

| Variable from NHIF Beneficiaries Records | Type | Category Breakdown |
| --- | --- | --- |
| Anonymized Identification Number | Numerical |  |
| Relationship To Policy Holder | Category | Principal, spouse, parent, child, other |
| Member Category | Category | Askari, Clerics, Councillor, Public Employee, Member of Parliament, Mutual-Principal, Private Employee, Private Individual,Retiree, Student and interns, toto afya kadi, KFW |
| Contribution | Numerical |  |
| Wealth Quintiles | Categorical drawn from numerical |  |
| Birthdate | Date |  |
| Gender | Category | Male, Female |
| Member enrollment Date | Date |  |

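### The cost of lacking social health protection is defined as a difference in incurred costs between self-selected groups, so care not sought counts as zero direct cost

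*Protocol*

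**What the plan says.** Research Question 1 (Protocol, Objectives and Research Aims) sets out to "quantify the direct and indirect cost associated with accessing NCD care services". It adds that the study will "determine the cost of not having social health protection by comparing the total costs incurred between NHIF beneficiaries, iCHF beneficiaries, and those" who belong to no scheme. It recognises that cover does not remove every burden, since for people with cover "their illness may still impose a social and economic burden in the form of missed work days and lost income".

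Analytical Methods starts from descriptive statistics. It then lists general hypotheses, among them "whether distance from a health facility moderates the association between social health protection and household health expenditure", which "will be explored using linear mixed models and analyses of variance". It names no model for the three-group cost contrast and does not say how care that was needed but not sought is treated.

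The household survey is to collect "household demographic and economic characteristics, health insurance and social protection, chronic illness, healthcare access and utilisation", along with expenditure, how out-of-pocket costs and premiums are paid, and productivity loss. Undiagnosed and untreated hypertension and possible diabetes are measured for Research Question 2.

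**The concern.** The wording promises an effect: what it costs a person not to be covered. The comparison offered is of costs actually incurred by people who are in NHIF, in iCHF or in neither. Two features separate the comparison from the promise.

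- **The groups are self-selected.** Annex I shows that NHIF membership goes by category, for example "Askari, Clerics, Councillor, Public Employee, Member of Parliament". Research Question 1 itself reports that people try to join another household's iCHF membership to escape out-of-pocket payment, so enrolment can follow expected spending.
- **Incurred cost is low for people who stay away.** Someone without cover who does not seek care has no direct cost. That person lowers the mean of the uncovered group, although going without care may be the main consequence of lacking cover.

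The second feature lies in the choice of outcome, so adding covariates does not remove it. The study is meant to inform health financing policy. A small or negative difference produced by people staying away could be read as showing that lacking cover costs little.

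**Working it through.** The plan attaches no figure to this comparison, so there is none to reproduce. The check is whether the stated quantity can miss its target, and what would have to hold for it not to. Apart from the 30,000 TZS in step 4, and the 32% overall coverage that step 3 is set to match, **all amounts below are assumptions**.

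**1. Forgone care alone, with comparable groups.** Let C0 be the cost per visit without cover, C1 the cost with cover, and u the use of care by people without cover relative to people with cover. The difference in incurred direct cost is D = u × C0 − C1. Take C0 = 20,000 TZS and C1 = 8,000 TZS.

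- u = 1: 20,000 − 8,000 = 12,000
- u = 0.5: 10,000 − 8,000 = 2,000
- u = 0.35: 7,000 − 8,000 = −1,000
- Sign change at u = 8,000 / 20,000 = 0.40

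**2. The offset from lost income.** Let L be the extra lost income recorded for each visit not made. Then D = u × C0 − C1 + (1 − u) × L. This equals the equal-use value C0 − C1 only if L = C0, here 20,000 TZS. With a smaller L the offset is partial; with a larger L it overshoots. Nothing in the protocol makes the two equal.

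**3. Forgone care and wealth together.** Assume half the population is poor and half rich. Coverage is 15% and 49%, which averages to the 32% in the Statement of Problem. Cost if care is used is 30,000 TZS (poor) and 60,000 TZS (rich), and cover cuts it by 40%. People without cover forgo a share f of care if poor and f/2 if rich.

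- Uncovered group: poor share 0.425 / 0.68 = 0.625, rich share 0.375.
- Covered group: poor share 0.075 / 0.32 = 0.234, rich share 0.766. Mean = 0.6 × (0.234 × 30,000 + 0.766 × 60,000), which is 31,781 with unrounded shares.
- Target at equal wealth and fully met need: 0.5 × 0.4 × 30,000 + 0.5 × 0.4 × 60,000 = 18,000.
- Unadjusted difference: 0.625 × 30,000 × (1 − f) + 0.375 × 60,000 × (1 − f/2) − 31,781.
- Wealth-standardised difference: 0.5 × 30,000 × (0.4 − f) + 0.5 × 60,000 × (0.4 − f/2).

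| f | Unadjusted difference (TZS) | Standardised for wealth (TZS) | Target (TZS) |
|---|---|---|---|
| 0 | 9,469 | 18,000 | 18,000 |
| 0.2 | 3,469 | 12,000 | 18,000 |
| 0.4 | −2,531 | 6,000 | 18,000 |
| 0.6 | −8,531 | 0 | 18,000 |

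Adjusting for wealth repairs the first row completely and the others only in part. If both strata cost 30,000 TZS (target 12,000), the standardised difference at f = 0.6 is 0.5 × 30,000 × (−0.2) + 0.5 × 30,000 × 0.1 = −1,500. The sign can therefore reverse even after adjustment.

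**4. Premiums.** The Household survey section gives 30,000 TZS as the cost of enrolling a household in the iCHF. Table 1 uses 30,000 TZS as the benchmark mean annual household health expenditure. Counting one enrolment or leaving it out moves an iCHF household's total by 30,000 / 30,000 = 100% of that benchmark. The protocol does not say whether total costs include premiums.

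**The case against.** The strongest reply is that Research Question 1 states an aim and not an estimator. Analytical Methods foresees linear mixed models for social health protection and expenditure, and its examples are only illustrative. Economic characteristics, chronic illness and utilisation are collected, and a covariate list may sit in a statistical analysis plan that is not at hand. This stands. A reader might infer that the comparison is raw and confounded by wealth, but the protocol never says it is unadjusted, and the lack of a covariate list is not the point.

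Non-use is also not ignored. The question concerns the cost of accessing care, the exit survey interviews only people who came for care, Research Question 2 studies people not in care, and lost work and income are counted. This stands in part. The exit survey cannot show those who stay away, the untreated-need results are never tied to the cost comparison, and the income offset is complete only by coincidence (step 2).

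Three further inferences are tempting and not supported:

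- **That NHIF members are mostly formal employees.** Annex I lists categories without proportions, and these include retirees, students and private individuals.
- **That there will be too few NHIF members to compare.** The protocol says "While the NHIF only insures approximately 7% of the population", a share of the population. It cannot be applied directly to households in two districts, and the exit survey of 1,632 patients adds members.
- **That this comparison is the main result of Research Question 1.** The protocol introduces it as an additional aim.

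**Conclusion.** The concern holds for the stated quantity and its causal wording. A comparison of incurred costs between self-selected groups does not determine the cost of lacking cover. Care not sought enters as zero direct cost, which pulls the contrast towards no cost of lacking cover. Under some assumed levels of forgone care it reverses the sign: below 40% relative use in the simple example, and somewhere between f = 0.2 and f = 0.4 in the unadjusted two-group example.

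The size of the bias in this study cannot be computed, because the documents give no cost by insurance status and no level of forgone care. The illustrations show that the sign is not protected; they do not show that it will reverse. They rest on the assumed costs and use rates, and on people without cover using less care, which the protocol does not quantify. The premium ambiguity needs no outside figure.

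**What to change.** - Restate the aim as an adjusted difference (an association) in direct and indirect costs between NHIF, iCHF and unprotected people among those with an NCD. Control for household economic status, need, distance and district.
- Beside it, report by insurance group the probability of using care and the proportion untreated (household survey), and direct and indirect costs among those who use care. Keep the indirect costs: out-of-pocket cost per visit alone would drop a component the protocol means to count, and it conditions on use.
- Show totals with and without premiums.
- State in advance that a small or negative cost difference will not be interpreted as a low cost of lacking cover without the utilisation results.

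The household survey section says that economic characteristics, insurance, chronic illness, utilisation and the way premiums are paid will be collected, so no new sampling is needed. The questionnaire is not shown, so the individual items should be checked. The price is slightly more analysis and a more modest claim.

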### Study Design

This study will use primary data that will be collected in two surveys: A general household survey including biometric testing for hypertension and diabetes, and an exit questionnaire administered to patients following their visit at a health facility.

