It is expected that with 2 field workers per health facility, 36 patients can be interviewed per day at hospitals and health centres, while 1 one field worker is expected to be able to interview 12 patients per day at each sampled dispensary. If patient volume is too low to meet this daily requirement, field workers will return later to the same facility to ensure the sample size is reached. As such, across both districts, we are anticipating a total sample size of 1,632 for the exit survey (Table 1), generously exceeding the minimum sample size that was previously indicated. Participants will be recruited while waiting to enter the consultation room, and the research assistant will administer the questionnaire after the participants has seen the clinician so as to avoid disrupting the work flow at the clinic.

The questions asked in the exit survey will mostly be the same as those asked in the household survey, so that household survey respondents will serve as the general population with which people accessing NCD care can be compared. However, in the exit surveys, additional questionnaire items will be included relating to the specific services being utilised on the day of the health facility visit. The questionnaire will take on average 20 minutes to complete. If during the piloting phase the questionnaire takes too long to complete, we will reduce the number of questions asked from the accepted survey, prioritizing questions that best reflect the explicit research questions.

**Table 1: Sample size and sampling strata.** Sample size calculated based on a hypertension prevalence of 19.9% (95% CI: 17.1-22.9) for rural Tanzania [11], population estimates from the Tanzania 2012 census, and a benchmark mean annual household health expenditure of 30,000 Tanzanian shillings by using a modified Cochran sample size calculation.

| **Study Type** | **Sample Size** | **Strata** |
| --- | --- | --- |
| Exit Interviews |  | Kilombero District:   - 18 health facilities |
|  | 72 per hospital | - 2 hospitals |
|  | 72 per health centre | - 8 health centres |
|  | 12 per dispensary | - 8 dispensaries |
|  |  | Same District:   - 18 health facilities |
|  | 72 per hospital | - 2 hospitals |
|  | 72 per health centre | - 8 health centres |
|  | 12 per dispensary | - 8 dispensaries |
|  | **Total: 1,632** | **Total: 36 health facilities** |
| Household Survey |  | Kilombero District: |
|  | 15 households | Ifakara town |

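### Research Question 2 asks for the undertreated proportion, but the planned analysis counts only people who are unaware or not in care and does not identify those in care with a raised reading

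*Protocol*

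**What the plan says.** The Protocol describes the same target in three ways.

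- Research Question 2: "We aim to identify the proportion of the population that remains undiagnosed, and undertreated for hypertension and diabetes".
- Household survey (under Sampling Strategy and Sample Size), for respondents who accept measurement: "we will also measure blood pressure and random blood sugar to quantify undiagnosed and untreated hypertension and possible diabetes in the population".
- Analytical Methods: the proportion of household respondents who are hypertensive or diabetic and "not aware of their condition or not enrolled in care".

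Undertreated is not defined anywhere. Study Design places the readings in one survey only: "A general household survey including biometric testing for hypertension and diabetes, and an exit questionnaire administered to patients following their visit at a health facility". After the proportion, Analytical Methods plans logistic regressions, whose purpose is given as: "identify differences between the household respondents with an NCD who are not enrolled in care and NCD patients from the exit interviews who are enrolled".

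**The concern.** Undertreated, untreated, and unaware or not enrolled are three different groups. The first, read literally, can include people who are in care and whose treatment is not sufficient. The planned count excludes anyone who is aware and enrolled, whatever the reading at the survey.

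At stake is whether the study can answer its own question. A person who never reached care and a person in care with a raised reading point to different problems in the health system. The Protocol's rationale mentions the quality of NCD care as well as access to it. The planned proportion describes only the first kind of problem. This is also not a detail that a later analysis plan would normally settle, because the Protocol itself fixes the numerator and that numerator does not match the question.

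**Working it through.** **Comparison of the passages.** Take a measured household respondent with hypertension and ask which target includes that person.

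| Respondent | Undertreated (Research Question 2, read literally) | Untreated (Household survey) | Unaware or not enrolled (Analytical Methods) |
|---|---|---|---|
| Raised reading, unaware | covered by undiagnosed | yes | yes |
| Aware, not in care | yes | yes | yes |
| In care, raised reading | possibly | no | no |
| In care, reading in range | no | no | no |

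The texts part in the third row. The second and third targets agree there; Research Question 2 is the one that differs.

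**Does another analysis fill the row?** The regressions compare household respondents not in care with exit-survey patients in care. They have no category for the reading among people in care. Study Design names no biometric testing in the exit survey, so exit patients could not be classed this way. Only the household survey can supply the row.

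**Denominator.** Analytical Methods does not say whether hypertensive or diabetic means a raised reading alone, or a raised reading or a known diagnosis.

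- Reading alone: everyone in care who counts as a case has a raised reading. The third row could then be had by subtraction, but only if the proportion is taken among cases. People in care with readings in range would drop out altogether.
- Reading or known diagnosis: the third and fourth rows are merged and cannot be separated.

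**Scale, as illustration only.** The Protocol states no figure for this point, so there is none to reproduce.

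Inputs from the Protocol:
- Prevalence: "Sample size calculated based on a hypertension prevalence of 19.9% (95% CI: 17.1-22.9) for rural Tanzania" (Table 1).
- Households: 390 per district, so 2 × 390 = 780. This matches 2 × (15 + 15 × 25) = 780. Table 1 prints 790, which would change the result below only from 155 to 157.

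Inputs assumed, because the documents do not give them:
- c, the share of hypertensive respondents in care: 0.1 to 0.5.
- u, the share of those with a raised reading: 0.3 to 0.7.
- One measured respondent per household and full acceptance of measurement.
- Everyone in care is aware, and 19.9% applies to a denominator that includes treated people. The Protocol does not show the case definition behind that figure.

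Expected hypertensive respondents: 780 × 0.199 = 155.2 (780 × 0.171 = 133 to 780 × 0.229 = 179 over the confidence interval).

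Among them:
- Planned proportion = 1 − c
- Proportion with the third row added = 1 − c + c × u
- People in the third row = 155.2 × c × u

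| c | u | Planned | With third row | People in third row |
|---|---|---|---|---|
| 0.1 | 0.3 | 90% | 93% | 155.2 × 0.03 = 4.7 |
| 0.3 | 0.5 | 70% | 85% | 155.2 × 0.15 = 23.3 |
| 0.5 | 0.7 | 50% | 85% | 155.2 × 0.35 = 54.3 |

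The difference, c × u, runs from 3 to 35 percentage points. Only its direction is independent of the assumptions: adding the third row can never lower the proportion.

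**The case against.** The strongest objection is that undertreated is one loosely chosen word. The second specific objective contrasts people engaged in care with people who are not, and Research Question 2 opens with the same contrast. The sentence that contains the word goes on to compare this group with patients who are accessing care. The Household survey section says untreated. On that reading the objective, the measurement and the analysis agree, and changing one word in Research Question 2 is enough. This is a fair reading and the documents do not rule it out. It changes which passage needs editing, but the passages would still need to be reconciled.

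A second objection also stands. A reading at a household visit does not by itself show that someone in care is undertreated. The Protocol calls the glucose result only possible diabetes and sends people with abnormal results to a provider for formal diagnosis. Putting the third row under the name undertreated would replace one mismatch with another.

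A reader might go further and infer that the plan treats enrolment as adequate treatment, or that it understates the care gap by a known amount. The documents support neither. Analytical Methods says nothing about the adequacy of care among those enrolled. The planned proportion is too low only if the target includes disease control among people in care, which is the unsettled point. The counts above rest on assumed shares with nothing in the documents to anchor them.

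**Conclusion.** The point holds in a limited form. As written, the analysis delivers the proportion undiagnosed or not in care. It does not identify household respondents in care with a raised reading, so Research Question 2, taken literally, is answered only in part. If untreated was meant, the fault lies in the wording of Research Question 2 and not in the analysis.

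This conclusion rests on comparing the texts and needs no numerical assumption. The size of the group left out is unknown; 5 to 54 people shows what is possible under the stated assumptions and is not an estimate. The case is firmer for blood pressure than for glucose. The point is worth acting on because the repair is small and needs readings and care status that the plan already calls for.

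**What to change.** In Analytical Methods, report measured household respondents in four rows:

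1. raised reading and unaware;
2. aware and not in care;
3. in care with a raised reading at survey;
4. in care with a reading in range.

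Define the denominator as a raised reading or a previous diagnosis or treatment. Keep the label of row 3 as given, without calling it proven undertreatment. Present blood pressure as the main result and random glucose as possible diabetes only. Use one term in Research Question 2, Household survey and Analytical Methods. If only untreated disease was intended, change the wording of Research Question 2 accordingly.

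The cost is a little extra analysis and a few definitions. Household respondents who accept are already measured, and the planned proportion already requires awareness and care status. The questionnaire is not shown here, so the team should check that it records previous diagnosis and current treatment well enough for rows 2 to 4. Row 3 will be imprecise if few respondents are in care, and single-visit readings will misclassify some people. Both limits should be stated beside the table.
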